### Ethics and Dissemination

The ethics review board at the University of Pennsylvania (institutional review board protocol no. 833854) and the Catalyst Foundation in India reviewed and approved this research protocol. The trial is registered with ClinicalTrials.gov (NCT04269824). All amendments and protocol modifications will be updated there. All enrolled study communities provided verbal consent to enroll in the study. Surveyed individuals provided informed consent. This consent process was conducted in the local language, Tamil. Participants will receive messages that may encourage them to improve their sanitation conditions or practices. Our assessment is that the benefits to study participation outweigh the minimal risks. Deidentified data will be used during analysis.

Research findings will be disseminated through presentations at conferences and submitted to peer-reviewed journals for open access. Our results will be shared with relevant local stakeholders through community-based meetings in participating wards through presentations made to the district and state level officials in Tamil Nadu.

### Data Monitoring, Reporting Harms, and Auditing

The research team ([name]) has text message groups and weekly calls with the implementation partner to discuss progress and issues from the field, including adverse events, so that prompt action can be taken. No harm is anticipated to the intervention recipients in this study. There are no plans for a data monitoring committee or audits for this trial.

## Results

This study completed its baseline survey in January 2020. Endline assessments are planned for July 2021. Results are anticipated to be published by the end of 2022.

## Discussion

This study will evaluate the effectiveness of the Nam Nalavazhvu intervention, a demand-side, descriptive norm- and network-centric intervention approach that aims to shift empirical expectations on targeted sanitation behaviors. Our behavior change communication approach employs dynamic signaling (ie, dissemination of descriptive information regarding others’ actual or intended improved sanitation practices) and reflects a strategy that is novel to the sanitation sector but which has been effective in changing a variety of behaviors, such as water use, drinking behavior, and energy consumption [36,44-46]. Evaluating the impact of such an approach may have widespread implications for policy and practice for sanitation programs in India and beyond if the intervention proves effective in improving sanitation behaviors via changing people’s empirical expectations. Our plan to also track normative expectations will also allow us to determine whether an intervention focused on shifting of empirical expectations has spillover effects on normative expectations.

Evidence from this study will address knowledge gaps regarding the application and effectiveness of a norm-diagnostic approach in the design of behavior change strategies that intervene upon the social determinants of collective sanitation behaviors. The intervention uses outreach workers and social media users to deploy most of its messages. Understanding the transmission of messages during household visits, peer learning sessions, and text messages will inform recommendations on the feasibility and effectiveness of using these platforms for norm-centric interventions. Insights generated in this study may generally contribute to the tools available to address descriptive norms for community-based interventions.

Limitations of this CRT include the use of wards as clusters in peri-urban communities. Although these are the smallest geographic operational units, some boundaries in specific districts were redrawn following the start of the intervention, leading to concerns about spillovers across buffer areas. Two critical country-specific incidences are impacting the implementation of the interventions. One is the highly contentious Citizens Amendment Act passed in December 2019 that led to nationwide protests in India. In our study, it led to refusals by households in predominantly Muslim wards, who resisted participating in any study that includes survey-based instruments. Secondly, the ongoing COVID-19 pandemic has led to considerable interruption in the implementation of group-level intervention activities. These aspects are being assessed through our process evaluation and will inform the interpretation of the results from this CRT.

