This study protocol summarizes the rationale and methods of a cluster-randomized trial (CRT; LENNS) that aims to evaluate the impact of a multilevel, demand-side behavior change intervention package called Nam Nalavazhvu on exclusive toilet use and maintenance. Prior studies have not explored norm-based intervention techniques specifically designed to change empirical expectations of sanitation behaviors in low-income communities. Findings from this multilevel intervention can be used to adapt them for other communities to shift norms around toilet use. There is limited evidence on whether intervening upon empirical expectations of others’ sanitation behaviors can lead to the emergence of normative expectations of toilet use. This type of phenomenon is theoretically plausible, and if demonstrated through this study, our findings can lead to insights to inform the design of norm-focused behavior change strategies [27,28]. Finally, our study is based in peri-urban communities, which will add to the currently limited sanitation literature regarding interventions that benefit peri-urban populations [29-31].

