### Theory and Evidence-Based Intervention Design

Empirical expectations can be powerful drivers of human behavior [34,35]. Norm nudging is a technique that aims to change the social expectations of an improved behavior of those around the respondent, preferably relevant social members [27]. The key assumption is that compliance is conditional or dependent on this change in expectation. Previous research to improve proenvironmental behaviors showed that telling individuals about their neighbors’ electricity consumption reduced their own usage [36]. Using similar techniques, another study successfully nudged hotel guests to reuse towels during their stay [37]. Evidence also suggests that descriptive norm messages are more effective when provided through personalized normative feedback than through broadcasting [38-40].

We synthesized the insights from our norm and social network assessment in Tamil Nadu to employ a systematic, multistep process to design the Nam Nalavazhvu intervention and used a theory of change approach to do so [41]. We used problem and solution tree analysis to depict causal streams of open defecation practices, including the sanitation-related social norms that supported these practices. We used theory and evidence to articulate the mechanisms through which change and maintenance of improved behaviors may occur. Based on the specific behavioral factors, we developed an intervention-mapping matrix and identified potential intervention techniques guided by Michie et al [42]. We acknowledged that norm compliance for individuals is influenced by household, community, and contextual factors by using a socioecological framework [43]. By 2019, SBM had increased coverage of toilets and had declared most states open defecation free [4]. We leveraged this context to disseminate descriptive norms information about those with improved sanitation practices in one’s community to shift empirical expectations and encourage others to conform to the norm of toilet use. We intentionally did not focus on techniques that use injunctive norms or perceived disapproval of others due to potential unintended negative consequences; to leverage personalized normative messages, we included techniques to engage community members across gender and age groups (Figure 3) [26].

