### Descriptive Information Dissemination and Capacity Building

To update empirical expectations regarding others’ improved sanitation practices, we will periodically collect information about sanitation practices from all households in study clusters. We will then disseminate related descriptive norm information during community events, household visits, and via text messages from peers in social groups. Action knowledge and social connections between ward members will be increased by connecting neighbors, outreach workers, and similar individuals in the ward who have adopted improved sanitation practices through events and activities. Information about available financial schemes, sanitation markets, and masons will be provided, and the outreach workers will assist in setting goals and taking steps to make progress towards them. Details of the activities are described in the following sections.

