#### Community Mobilization and Commitment Events

Participants will include influential political and community leaders to applaud exclusive toilet users and promote improved sanitation practices. Messages will highlight the change happening in their communities and the benefits of using a toilet for families, and facilitate a public commitment to exclusive toilet use. These messages will reinforce those heard by residents through other group and household activities.

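### The two-arm contrast identifies the whole package's effect on normative expectations, not spillover from empirical expectations as the Discussion says

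*Protocol article*

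**What the plan says.** The Discussion states that following normative expectations will allow the team to determine "whether an intervention focused on shifting of empirical expectations has spillover effects on normative expectations". The Study Rationale in the Introduction notes limited evidence on "whether intervening upon empirical expectations of others’ sanitation behaviors can lead to the emergence of normative expectations of toilet use" and continues: "This type of phenomenon is theoretically plausible, and if demonstrated through this study", the findings could inform later norm-focused strategies.

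The Secondary Outcomes section defines normative expectations as beliefs about what others think one should do, and empirical expectations as beliefs about what others do. Both belong to the same secondary outcome.

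On the content of the package, Theory and Evidence-Based Intervention Design says: "We intentionally did not focus on techniques that use injunctive norms or perceived disapproval of others". Community Mobilization and Commitment Events says: "Participants will include influential political and community leaders to applaud exclusive toilet users and promote improved sanitation practices". The same section adds that the event messages are to bring about a public pledge of exclusive use. Descriptive Information Dissemination and Capacity Building adds practical help: "Information about available financial schemes, sanitation markets, and masons will be provided".

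On design, the Study Design section describes two arms: the full package against no active study intervention, surveyed at baseline and at one year. Statistical Analyses plans an intention-to-treat comparison of the arms.

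**The concern.** Spillover from empirical to normative expectations means that beliefs about approval moved because beliefs about behaviour moved. A randomised comparison can show this only if the package has no other way of moving beliefs about approval. Here it has one. When respected leaders applaud exclusive users in public, residents learn directly what influential people think one should do, and that is the outcome being measured.

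If normative expectations rise in the intervention arm, a reader of the Discussion would take this as evidence that descriptive information alone can produce a normative expectation. The Study Rationale offers that mechanism as a basis for designing later programmes. A programme that kept the descriptive messages and dropped the leader events could then rest on an effect the trial had not isolated.

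**Working it through.** The article gives no figure for this claim, so there is none to reproduce. The check sets what the claim needs beside what the design supplies, then shows the algebra.

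**What the claim needs and what the design supplies**

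| Needed to attribute a change in normative expectations to empirical expectations | What the article gives |
|---|---|
| No direct route from package to normative expectations | Leaders applaud exclusive users and facilitate public commitment (Community Mobilization and Commitment Events) |
| Or an arm with descriptive information only | Two arms, whole bundle against no active study intervention (Study Design) |
| Or, at the least, measurements that order the two changes in time | Baseline and one endline, both outcomes in the same survey (Study Design; Study Outcomes and Measures) |
| An analysis aimed at the pathway | Intention-to-treat difference between arms (Statistical Analyses); the article states no pathway analysis |

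The last row is not itself a fault, since such an analysis could sit in a document not shown. It would not be the randomised contrast in any case.

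**Algebra**

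Let *a* be the arm effect on empirical expectations, *b* the effect of empirical on normative expectations, and *d* the package's effect on normative expectations by any other route, such as public approval. In a linear model:

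arm difference in empirical expectations = *a*

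arm difference in normative expectations = *d* + *a* × *b*

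The two arm differences supply two equations for three unknowns. With effect sizes assumed purely for illustration and *a* = 0.5 throughout:

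- all through empirical expectations (*b* = 0.4, *d* = 0): 0 + 0.5 × 0.4 = 0.20
- half and half (*b* = 0.2, *d* = 0.1): 0.1 + 0.5 × 0.2 = 0.20
- none through empirical expectations (*b* = 0, *d* = 0.2): 0.2 + 0.5 × 0 = 0.20

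All three cases give the same pair of arm differences, 0.5 and 0.20. Seeing both expectations rise does not tell full spillover from none.

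**Could a further analysis separate them?**

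Regressing normative expectations on arm and empirical expectations would give estimates of *b* and *d*. But empirical expectations are not randomised within an arm, and both beliefs come from the same respondent in the same survey. The estimates would rest on there being no unmeasured common cause of the two beliefs and no influence running from normative to empirical expectations. Randomisation secures neither. The qualitative rounds at 3 months, 6 months and 1 year can help with interpretation, but they use purposively selected respondents and do not supply the missing contrast.

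**The case against.** The strongest reply is that the Discussion, read word for word, asks whether an intervention focused on empirical expectations also affects normative ones. The randomised contrast does estimate that. The operative sections agree: the Specific Aims speak of the impact of the intervention on both kinds of expectation, Secondary Outcomes lists them together, and Statistical Analyses plans arm differences. The Study Rationale describes a gap and a conditional possibility. It does not promise a result and does not mention tracking.

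Much of this stands. The fault lies in one Discussion sentence and one Introduction remark, not in the aims or the analysis. But *spillover*, together with the causal wording of the Study Rationale, leads a reader to the attributional meaning, and the article does not warn that the leader events undercut it.

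A reader might also infer more than the documents support:

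- *That the design section is contradicted by the leader events.* It says only that injunctive techniques were not a focus, on account of possible negative consequences. It does not say that approval content is absent, so it needs no correction.
- *That wall slogans and stickers are also approval messages.* Both can be read as descriptive signals that others already own and use toilets. Public pledges too reveal intended behaviour, which the Discussion counts as descriptive information. Leader applause is the one clear approval route, and it is enough.
- *That the article claims any rise in use will act through empirical expectations.* That Discussion sentence is conditional. The practical help in the package is a reason for care in interpreting a rise in use, but no such conclusion has been announced.

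**Conclusion.** The point holds as a matter of identification and wording. The trial can estimate the effect of the whole package, including its public-approval and commitment events, on normative expectations. It cannot determine whether shifting empirical expectations produced that effect.

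This rests on one assumption: that leaders' public applause can change what residents believe others think one should do. Given the article's own definition of the outcome, that is hard to dispute.

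No numerical size can be attached. It may be tempting to put a range on the share of the effect due to each route, but the documents give nothing from which to calculate one, and a full range would only repeat that the share is not identified. The consequence is limited to the interpretation of a secondary outcome. The primary comparison, the sample size and the fieldwork are untouched.

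**What to change.** 1. Reword the Discussion sentence and the Study Rationale remark so that they claim the effect of the whole package on empirical and normative expectations, naming the leader-led approval and commitment events as part of it. This brings them into line with the Specific Aims.
2. Label any analysis that links empirical expectations to normative expectations, or to toilet use, as exploratory and dependent on assumptions that randomisation does not secure.
3. Adjust each expectation outcome for its own baseline value. Statistical Analyses only considers adjusting for variables found imbalanced. The baseline survey preceded randomisation and the outcomes are evaluated at baseline, so the values are already in hand. Respondents recruited as replacements at endline (Data Collection) have no baseline of their own, so use the ward's baseline mean for them. This is for precision and does not resolve the attribution problem. The article gives no baseline-endline correlation for the expectation measures, so the gain is not quantified here.

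The cost is wording and one analysis specification, with no change to fieldwork. The downside is a less ambitious secondary claim.

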## Appendix

Multimedia Appendix 1 Study wards enrolled in each town panchayat, Tamil Nadu, India, 2020.

Multimedia Appendix 2 Outcome measures.

## Abbreviations

BCD: Behavior Centered Design
CLTS: Community-Led Total Sanitation
CRT: cluster-randomized controlled trial
CSNBD: Center for Social Norms and Behavioral Dynamics
LENNS: Longitudinal Evaluation of Norms and Network Study
RANAS: Risks, Attitudes, Norms, Abilities, and Self-regulation
SBM: Swachh Bharat Mission
SNT: social norms theory
WHO-5: The 5-item World Health Organization Well-Being Index
